##### Secondary outcome measures

The secondary outcome measures will include several commonly used measures of specific domains of cognitive function, sleep quality, and physical activity level. The measures of specific domains of cognitive function (memory, language, executive function, and visuospatial skills) will comprise the Auditory Verbal Learning Test (AVLT) [57], Category Verbal Fluency Test (CVFT) [58], Boston Naming Test (BNT) [59], Shape Trail Test (STT) [60], Digital Span Test (DST) [61], and Rey-Osterrieth Complex Figure Test (ROCFT) [62]. The Pittsburgh Sleep Quality Index (PSQI) [63] will be used to measure sleep quality, and the Berg Balance Scale (BBS) [64] and ADL will be used to measure the physical activity level. More information about the sensitivity and specificity of the assessment methods etc. can be found from the reference cited.

#### Blood biomarkers parameters

Before and after the intervention (in the morning after a 12-h fast), 5 mL whole blood will be collected into a polypropylene tube containing ethylenediaminetetraacetic acid (EDTA) from each participant’s antecubital vein by a registered nurse. The samples will immediately be centrifuged at 4000 rpm for 5 min at 23 °C (5810R Centrifuge, Eppendorf). The plasma will be aliquoted and stored at − 20 °C. Thereafter, the plasma levels of BDNF, IL-6, TNF-α, Aβ, and phosphorylated tau will be measured by enzyme-linked immunosorbent assays. The procedures will use the same types of assay kit and laboratory instruments, and they will be performed by the same laboratory technician to avoid inter-operator bias.

#### Event-relate potential P300

A Natus Dantec™ Keypoint Focus 8-channel system (Natus Medical Incorporated) will be used to record and analyze brainstem auditory ERP-P300 data. Each participant will sit in a comfortable chair in a sound-attenuated room with a warm light. Based on the international 10–20 system of electrode placement, central (Cz), parietal (Pz), and frontal (Fz) electrodes will be used for continuous recording; the right mastoid will serve as the reference electrode site. The auditory oddball paradigm, which consists of a series of standard (1000 Hz) and deviant (2000 Hz) tones, will be delivered binaurally through a headset. The sound level for each tone will be 110 dB, with a bandwidth of 0.5–20 Hz, a duration of 50 ms, and an inter-stimulus interval of 800 ms on average. All recordings will be performed with electrode impedances < 5 kΩ. The deviant tones will make up 20% of the tones and each of the three rounds of testing average count 20 stimuli. Each participant will be instructed to close their eyes, keep awake and concentrate, and press the button as accurately and quickly as possible when they hear the deviant sounds. Each participant will perform a pre-test first to make sure that they have understood the task. P300 latency (mV) and amplitude (ms) are key factors used for analyzing ERP data. Also, the reaction time (ms) is defined as the length between hearing a deviant tone and pressing the button.

#### MRI parameters

Multimodal MRI scans will be acquired at baseline and immediately after the intervention using a 3.0 T Prisma scanner (Siemens, Erlangen, Germany) in the same scan modes, which will involve structural MRI (sMRI), resting-state fMRI (rs-fMRI) and task-state fMRI (ts-fMRI). High-resolution T1-weighted images of the whole brain will be obtained using a sagittal 3D magnetization-prepared rapid gradient echo (MP-RAGE) sequence. Rs-fMRI will be performed using a multiband echo-planar imaging sequence. Ts-fMRI will comprise a scan involving memory and executive tasks. The scan sequence details are displayed in the Additional file. Quality-control checks on the phantom and imaging sequences will be performed before data collection. Image quality will be validated by an experienced imaging specialist. Individuals with potential cerebral impairments or structural abnormalities revealed by MRI will be excluded from subsequent experiments (e.g., rs-fMRI scan and ts-fMRI scan).

### Data collection and analysis

All data analysis will be performed using SPSS Statistics v22.0 (IBM). To ensure that the outcome assessors and data analysts are blinded to group assignment, they will not interact with the participants except, in the case of outcome assessors, during data collection. Demographic and other baseline characteristics will be summarized using descriptive statistics. If necessary, the results will be adjusted for potential confounders, such as age, gender, and education. Between- and within-subject comparisons of the neuropsychological test scores and other outcomes will be conducted using repeated-measures analysis of variance (ANOVA). Statistical analyses will be based on an intention-to-treat (ITT) approach [65], missing data will be imputed by multiple imputation. *P* < 0.05 for two-tailed tests will be considered significant. In sensitivity analyses, we will perform per-protocol (PP) analyses [66], including only the participants who completed the SIACI program and outcome assessment. The details of the fMRI data analysis are displayed in the Additional file.

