#### Sample size determination

The required sample size was estimated using PASS v11.0 (NCSS, Kaysville, UT, USA) based on a completely random design for comparing the means of two independent samples. To our knowledge, there is no previous study on a comprehensive intervention for CIs among older adults in mainland China, so we estimated the effect size of one of the primary outcomes (general cognitive function) based on our previous study that used creative expression therapy to improve MCI patients’ cognitive function [46] . The study was like the planned trial in some respects, as both are RCTs, one of the primary outcomes is general cognitive function, and one of the primary outcome measurement tools (MoCA) is the same. Our previous study [46] found MoCA scores of 24.68 ± 1.84 and 23.13 ± 1.68 in the intervention and control groups, respectively. A sample size of 35 participants per group was determined to be sufficient to detect an effect with a type 1 error rate of 5% (α = 0.05) and 95% power (β = 0.05). Taking into consideration a 20% attrition rate, a total of 88 participants will be needed, with 44 participants per group.

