#### Demographic and other baseline characteristics

To determine whether demographic and other baseline variables are confounding factors that affect the outcome variables, basic demographic data (e.g., age, gender, religion, marital status, education, occupation, and socioeconomic status), history of disease, medication use, and leisure activities will be collected from participants via a questionnaire at baseline.

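### The repeated-measures ANOVA names no treatment test, covariate adjustment is conditional and open-ended, and a prespecified model adjusted for baseline score and diagnostic stage would be a cost-free improvement

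*Protocol article*

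**What the plan says.** Three sections of the protocol article bear on this point.

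- **Data collection and analysis** sets the model: "Between- and within-subject comparisons of the neuropsychological test scores and other outcomes will be conducted using repeated-measures analysis of variance (ANOVA"). It then sets the covariate rule: "If necessary, the results will be adjusted for potential confounders, such as age, gender, and education". Tests are two-sided at the 5% level, and data analysts are blinded to allocation.
- **Demographic and other baseline characteristics** gives the purpose of collecting the baseline variables: "To determine whether demographic and other baseline variables are confounding factors that affect the outcome variables".
- **Sample size determination** sizes the trial "based on a completely random design for comparing the means of two independent samples", that is, without a baseline score or any covariate.

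Outcome measures lists three occasions: baseline, immediately after the intervention, and 6 months. Inclusion criteria admit SCD, MCI and mild AD. Diagnostic criteria define these stages partly by MoCA and MMSE scores, and both scales are among the primary outcomes. The randomisation section gives a 1:1 ratio and mentions no stratification.

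**The concern.** Two things are left loose in what the article does state.

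**The covariate rule.** Adjustment depends on an undefined necessity, and the list is only illustrative. Read with the stated purpose of the baseline data, the natural interpretation is that confounder status will be judged from the trial's own data. In a randomised trial any baseline imbalance arises by chance. The sound reason to adjust is precision, and the set should be fixed beforehand. Diagnostic stage is tied by definition to the level of MoCA and MMSE, so it is a plausible strong predictor of outcome, yet it is not among the examples.

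**The treatment test.** A three-visit repeated-measures ANOVA offers several tests:

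- The group main effect averages in the baseline visit, where randomisation makes the expected difference zero. A sustained effect is therefore reduced to two thirds.
- The group-by-time term is a valid randomised comparison, but it is a 2-df test of any difference in profile. It does not by itself estimate a difference at a named visit.
- The time effect within an arm is not a randomised comparison.

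None of these is the comparison of two means on which the trial was sized. At stake are the clarity of the main estimate, some power, and the freedom to choose covariates late.

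**Working it through.** **Inputs from the protocol article**

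- "MoCA scores of 24.68 ± 1.84 and 23.13 ± 1.68 in the intervention and control groups, respectively": difference 24.68 − 23.13 = 1.55; pooled SD √((1.84² + 1.68²)/2) = 1.762; d = 1.55/1.762 = 0.88.
- "type 1 error rate of 5% (α = 0.05) and 95% power (β = 0.05"); two-sided, since P < 0.05 "for two-tailed tests will be considered significant".
- "A sample size of 35 participants per group was determined to be sufficient"; 20% attrition; 88 in total.

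**Assumptions (the article gives no figure)**

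- Correlation r between visits, taken as 0.3, 0.5, 0.7 and 0.8.
- Equal variances and equal correlations at all visits.
- A sustained effect, pattern (0, d, d), unless stated otherwise.

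**Step 1: the plan's own figure.** For an unadjusted two-sample t test with n = 35 per group, the noncentrality is 0.88 × √(35/2) = 3.68, and power is 95.2%. With n = 34 it is 94.7%. So 35 per group reproduces. Then 35/0.8 = 43.75, rounded up to 44 per group and 88 in total, also reproduces.

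**Step 2: power of the candidate tests at 35 per group**

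- Group main effect: difference (2/3) × 1.55 = 1.033, SD 1.762 × √((1 + 2r)/3), t with 68 df.
- Group-by-time: λ = (n/2) × Σ(eₜ − ē)² / (SD²(1 − r)), where eₜ is the group difference at visit t; F with 2 and 136 df. For (0, d, d) the sum is (2/3) × 1.55².
- Baseline-adjusted ANCOVA at the post-intervention visit: difference 1.55, SD 1.762 × √(1 − r²), t with 67 df.

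| r | Group main effect | Group-by-time | ANCOVA |
|---|---|---|---|
| 0.3 | 91.2% | 89.9% | 96.7% |
| 0.5 | 84.2% | 97.2% | 98.7% |
| 0.7 | 77.2% | 99.9% | 99.9% |
| 0.8 | 73.8% | >99.9% | >99.9% |

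The main effect misses the planned 95% at every r. Group-by-time misses it only at r = 0.3.

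**Step 3: a fading effect.** If the effect halves by 6 months, the pattern is (0, d, d/2) and the sum falls to 1.55²/2. At r = 0.3, λ = 17.5 × 1.201/(3.104 × 0.7) = 9.68, and group-by-time power is 79%. ANCOVA at the post-intervention visit is unaffected at 97%.

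**Step 4: a wider SD.** The planning SDs come from a study in MCI alone, while this trial mixes three stages. If the SD were 3.0 (an assumption), with a sustained effect:

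| r | Group main effect | Group-by-time | ANCOVA |
|---|---|---|---|
| 0.3 | 49% | 45% | 61% |
| 0.7 | 36% | 82% | 85% |

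**Step 5: the worst case for free covariate choice.** A simulation used 35 per group, three independent covariates, no treatment effect and 8,000 runs. Any significant result among the 2³ = 8 possible covariate sets was counted. Two-sided type I error rose from about 5% to 8%, 11% and 14% when the covariates jointly explained 10%, 30% and 50% of the variance. This is an upper illustration of what the wording permits, not a forecast.

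**The case against.** The strongest case for the plan is this. Repeated-measures ANOVA is a valid analysis, and in a pre/post/follow-up design the usual treatment test is group-by-time, which is a randomised comparison of change. On the protocol's own effect size that test has at least 97% power once r reaches 0.5, and at r = 0.7 it equals ANCOVA. Analysts are blinded. The covariate list is illustrative, so diagnosis is unnamed rather than excluded. A separate analysis plan may fix the model terms and the contrast.

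Much of this stands, and it rules out four stronger readings that a reader might infer:

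- *Baseline score is left out of the model.* It is not: baseline is one of the three levels of time. It is absent only as a covariate.
- *The plan uses a test diluted by a third.* That is true only of the group main effect, which the article does not designate as the treatment test.
- *Covariates will be picked after results are seen.* The wording permits this and the baseline-characteristics section leans towards it, but no such procedure is stated.
- *The trial is underpowered because it does not adjust.* The 35 per group and 88 in total reproduce without any covariate.

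What the objection does not remove is that the conditional rule is written into the article and is not mere silence. Blinding limits steering towards a favoured arm. It does not stop an analyst with coded groups from seeing which covariate set gives a significant difference.

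**Conclusion.** The point holds as a recommendation to tighten the primary analysis, not as an error that must be corrected. The adjustment rule has no criterion and no closed list, the treatment term is not named, and neither baseline score nor diagnostic stage is named as a covariate.

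The size depends on which term is tested. Against baseline-adjusted ANCOVA at d = 0.88 and a sustained effect, the group main effect loses about 5 percentage points at r = 0.3 (91.2% against 96.7%) and about 26 at r = 0.8. Group-by-time loses about 7 points at r = 0.3, 1.5 at r = 0.5 and nothing that matters from 0.7 upwards. Its loss grows to about 18 points at r = 0.3 if the effect halves by 6 months.

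These figures rest on the assumed correlations, equal variances and correlations across visits, and the assumed effect patterns. They count the gain from baseline score alone. Any further gain from diagnostic stage is not quantified, and it may be partly absorbed by baseline MoCA.

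**What to change.** Replace the conditional sentence and name one primary analysis:

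- Use ANCOVA, or a mixed model for the two post-baseline visits with visit, group-by-visit, baseline score and baseline-by-visit.
- Always include baseline score, diagnostic stage (SCD, MCI, mild AD), age and education, and delete *if necessary*.
- Make the adjusted between-group difference in MoCA immediately after the intervention the primary contrast, with the 6-month difference as a second contrast. MoCA is the natural choice because it is the scale on which the trial was sized.
- Report within-arm change as descriptive only.

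The cost is wording. Baseline scores, diagnosis, age and education are already collected, the named software fits these models, and the sample size need not change.

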#### Randomisation, allocation concealment, and blinding

Ensuring allocation concealment, participants will be randomized (after obtaining written informed consent, eligibility screening, and baseline assessment) to the SIACI and waitlist control groups at a 1:1 ratio by a study staff member (who will not be involved in participant recruitment or outcome assessment) using Research Randomizer software (http://www.randomizer.org/). The participants will then be told their group assignment by the intervention staff. Due to the nature of non-pharmacological interventions, only the outcome assessors and data analysts (not the participants or intervention staff) will be blinded to group allocation.

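### The only named sensitivity analysis, limited to completers, cannot test the assumption behind the multiple imputation

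*Protocol article*

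**What the plan says.** The section on data collection and analysis fixes two choices. The primary approach is given as "Statistical analyses will be based on an intention-to-treat (ITT) approach [65], missing data will be imputed by multiple imputation". The sensitivity analysis is per-protocol, "including only the participants who completed the SIACI program and outcome assessment". No other sensitivity analysis is named.

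The sample size section expects loss: "Taking into consideration a 20% attrition rate, a total of 88 participants will be needed, with 44 participants per group". The outcome section sets assessments at baseline, straight after the intervention and at 6 months. The waitlist section has controls carry on as usual for 16 weeks, so they have no programme to stop during that period. The discussion lists ITT analysis among the trial's protections against bias.

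The article does not say whether people who stop SIACI are still assessed, nor does it give the imputation model. An article may leave such details to a fuller plan, so their absence is not the point here. The point is the sensitivity analysis that the text does name.

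**The concern.** A sensitivity analysis for missing data should change the assumption about the unseen outcomes and show whether the conclusion survives. The per-protocol analysis does not do this. It removes the people whose outcomes are in doubt and keeps those whose outcomes are known.

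Ordinary multiple imputation with arm in the model fills in missing SIACI scores from SIACI participants who stayed. If the missing people had stopped the programme, this credits them with the benefit of those who continued. The per-protocol analysis estimates the benefit in those who continued. The two results would then agree whether or not the imputation assumption is true.

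What is at stake is interpretation. Close agreement could be read as robustness, and an effect in completers could be reported as the effect of being assigned to SIACI.

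**Working it through.** **Inputs from the article**
- Planning figures: "MoCA scores of 24.68 ± 1.84 and 23.13 ± 1.68 in the intervention and control groups".
- Error rates: "type 1 error rate of 5% (α = 0.05) and 95% power (β = 0.05"), with P < 0.05 "for two-tailed tests will be considered significant".
- Evaluable number: "A sample size of 35 participants per group was determined to be sufficient".
- Allocation: "to the SIACI and waitlist control groups at a 1:1 ratio".
- Attrition allowance: 20%.

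**Assumptions made here**
- The 1.55-point difference is the effect in completers.
- The 20% lost in the SIACI arm are all people who stopped.
- Stoppers keep a share k of the benefit (k from 0 to 1).
- Stopping is otherwise unrelated to outcome.
- The control side of the completers' set is the controls with an outcome assessment, since they have no SIACI to complete during the comparison.

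**Step 1: the plan's own figure**

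Difference = 24.68 − 23.13 = 1.55. Pooled SD = √[(1.84² + 1.68²)/2] = 1.762. Standardised effect = 1.55/1.762 = 0.88.

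The two-sided noncentral t calculation gives power 0.947 with 34 per group and 0.952 with 35, so 35 is reproduced. Then 35/(1 − 0.20) = 43.75, rounded up to 44 per group, 88 in total. The sample size is sound.

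**Step 2: effect in everyone randomised**

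Effect = 1.55 × [(1 − 0.20) + 0.20 × k]. If stoppers are unassessed, missing-at-random imputation by arm and the completers' analysis both target 1.55.

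| Share kept (k) | Effect in all randomised | Excess of 1.55 over it | Relative excess |
|---|---|---|---|
| 0 | 1.55 × 0.80 = 1.24 | 0.31 | 0.31/1.24 = 25% |
| 0.5 | 1.55 × 0.90 = 1.395 | 0.155 | 0.155/1.395 = 11% |
| 0.75 | 1.55 × 0.95 = 1.473 | 0.077 | 5% |
| 1 | 1.55 | 0 | 0% |

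**Step 3: simulation check**

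Set-up: 44 per arm, 20% missing in each arm, 10 imputations, 1,500 runs, baseline–outcome correlation 0.5 (assumed), difference in mean score after the intervention. This is simpler than the planned repeated-measures ANOVA.

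| Scenario | Imputed estimate | Completers' estimate | True effect, all randomised |
|---|---|---|---|
| Unassessed, arm in model, k = 0 | 1.53 | 1.53 | 1.22 |
| Unassessed, arm in model, k = 0.5 | 1.55 | 1.55 | 1.40 |
| Unassessed, arm in model, k = 1 | 1.55 | 1.55 | 1.55 |
| Unassessed, arm left out of model, k = 0 | 1.23 | 1.55 | 1.23 |
| Unassessed, arm left out of model, k = 1 | 1.24 | 1.56 | 1.56 |
| Stoppers still assessed, k = 0 | 1.24 | 1.56 | 1.24 |

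In the first three rows the two analyses agree whether the truth is 1.22, 1.40 or 1.55, so their agreement carries no information about k. With no treatment effect at all, the imputed estimate averaged 0.02 and the rejection rate was 5.2%.

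**The case against.** The strongest reply is that the bias is conditional and the article fixes none of its conditions. It needs stoppers to be unassessed, imputation by arm under missing-at-random, and stoppers to keep less benefit than completers. The per-protocol rule lists finishing the programme and finishing the assessment as separate requirements. That fits a plan in which someone stops SIACI and is still tested. Such scores would enter the ITT analysis as observed. The estimate would then be right, and the completers' result would visibly differ from it (1.24 against 1.56). If arm were left out of the imputation model there would be no overstatement either, although the effect would be understated when benefit is kept. All of this stands.

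Three stronger readings are tempting, and the document does not support them:
- A reader might infer that the planned ITT estimate is overstated. That would follow only if all three conditions held.
- A reader might take the 20% as the rate of stopping SIACI. It is a sample-size allowance applied to both arms, and controls have no SIACI to stop during the comparison. The text also provides mailed materials, WeChat contact and phone guidance if group sessions are suspended, so missing a group session need not mean stopping.
- A reader might infer that someone who leaves early has no assessment date. The design and waitlist sections set 16 weeks for both arms, and the table of assessment times is not shown here.

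It can also be said that the imputation model and any missing-not-at-random analysis belong in a fuller plan. That is fair for the model. It does not answer the narrower point: the article chose a sensitivity analysis, and that analysis cannot examine the imputation assumption when stoppers are lost.

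**Conclusion.** The point holds in conditional form. If people who stop SIACI are lost and imputed by arm under missing-at-random, the primary analysis and the only named sensitivity analysis target the same completers' effect, and the second cannot check the first.

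On the planning figures, with all of the 20% lost in the SIACI arm assumed to be stoppers, the excess over the effect in everyone randomised lies between 0 and 0.31 MoCA points. The top of that range requires that no stopper keeps any benefit, however many sessions were attended. The bias scales with a real benefit: in the set-up tested, stopping created no false effect where there was none. Dropout related to outcome was not modelled.

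This is a worthwhile and inexpensive improvement. It does not show that the planned estimate is wrong.

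**What to change.** 1. State that all randomised participants, including those who stop SIACI, are invited to the existing 16-week and 6-month assessments, and that their scores enter the ITT analysis as observed.
2. Keep the per-protocol analysis if wanted, but supplement it with a missing-data sensitivity analysis. One option is control-based multiple imputation, which draws missing SIACI scores from the waitlist arm's distribution. The other is a delta-adjusted (tipping-point) imputation, which lowers the imputed SIACI scores step by step until the conclusion changes. Control-based imputation itself assumes that stoppers resemble controls, so read it as a cautious case. Present it beside the primary result.

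The cost is some wording, effort to recall up to about 9 people per arm (44 − 35) at assessments already planned, and one extra analysis. The reported effect may turn out smaller.

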**Methods:**

The planned study is a single-center, parallel-arm, randomized controlled trial with allocation concealment and outcome assessor blinding. A total of 88 participants will be randomized to two groups: (i) an intervention group that receives the 16-week, 24-session SIACI program and (ii) a waitlist control group (which will receive the SIACI program after completing the follow-up assessment). Global cognitive function, specific domains of cognition (memory, language, executive function, and visuospatial skills), and other health-related outcomes (quality of life, anxiety, depression, sleep quality, and physical activity level) will be measured at baseline, immediately after the intervention, and at the 6-month follow-up. Blood biomarkers, event-related potential (ERP)-P300, and magnetic resonance imaging (MRI) data will be collected at baseline and immediately after the intervention to explore the mechanisms of SIACI.

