### Waitlist control group

Following baseline assessment, participants in the waitlist control group will engage in their usual activities during the 16-week study period. After the study, if the SIACI program leads to significant improvements in cognitive function, these participants will be offered the program as a courtesy for their participation.

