### Outcome measures

To explore the effects and mechanisms of SIACI, various measurements will be obtained at baseline, immediately after the intervention, and at the 6-month follow-up. Outcome measures will include neuropsychological assessments, blood biomarkers, ERP-P300, and MRI parameters. All outcome measures and assessment time points are shown in Table 1. The outcomes will be assessed by experienced staff members who will be blinded to group allocation throughout the study.

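### The per-protocol rule requires completing SIACI, which waitlist controls cannot do before the compared outcomes are measured; as probably intended, it filters on adherence in one arm only

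*Protocol article*

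**What the plan says.** Under Data collection and analysis, the protocol article plans between- and within-subject comparisons by repeated-measures ANOVA. The main analysis set is stated: "Statistical analyses will be based on an intention-to-treat (ITT) approach [65], missing data will be imputed by multiple imputation". The one sensitivity analysis named there is per-protocol: "we will perform per-protocol (PP) analyses [66], including only the participants who completed the SIACI program and outcome assessment". The two conditions are joined and apply to all participants alike.

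The abstract's Methods paragraph describes the comparator as "a waitlist control group (which will receive the SIACI program after completing the follow-up assessment"). The Waitlist control group section says that "participants in the waitlist control group will engage in their usual activities during the 16-week study period", and adds: "After the study, if the SIACI program leads to significant improvements in cognitive function, these participants will be offered the program". Under Outcome measures, "various measurements will be obtained at baseline, immediately after the intervention, and at the 6-month follow-up".

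**The concern.** A per-protocol set has to be definable in both arms, because its purpose is to compare those who followed their assigned regimen. Here the entry condition is completion of a programme that one arm does not receive while outcomes are being compared. Either the analysis cannot be run as a comparison, or someone must supply a rule for controls that the text does not contain, possibly after data have been seen.

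The obvious repair is to ask controls only for completed assessments. That leaves an imbalance: staying with 24 sessions over 16 weeks removes people from the SIACI arm, and controls face no equivalent demand. If those who stay would have scored differently anyway, the two filtered groups are no longer comparable by randomisation. Agreement between this analysis and the intention-to-treat result would then be weak evidence of robustness, and it is the only such check the article names.

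**Working it through.** **1. The plan's own figures.** Sample size determination gives MoCA 24.68 (SD 1.84) against 23.13 (SD 1.68), two-group comparison, α = 0.05, 95% power, 20% attrition.
- Difference = 24.68 − 23.13 = 1.55.
- Pooled SD = √((1.84² + 1.68²)/2) = √3.104 = 1.762.
- Two-sided t-test power is 0.947 at 34 per group and 0.952 at 35, so 35 per group reproduces.
- 35/0.8 = 43.75, rounded up to 44 per group and 88 in total. This also reproduces.

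The point does not depend on the sample size. These figures only supply the arm size and the MoCA scale used below.

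**2. Literal reading.** Entry requires SIACI completed and outcomes assessed. By the abstract, controls start SIACI after the follow-up assessment; by the Waitlist control group section, after the study. Neither allows a control to have completed it by the post-intervention assessment. The set is then 0 of 44 controls and, if 20% of the SIACI arm did not complete, about 44 × 0.8 ≈ 35 SIACI participants. There is no between-group contrast.

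**3. Probable reading.** Conditions by arm:
- SIACI: assessments completed, and programme completed.
- Control: assessments completed.

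The assessment filter is common to both arms. The adherence filter is not.

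**4. Illustration of size.** Assumptions, none of them trial figures: no true effect; 20% of the SIACI arm excluded; no control loss; outcome and propensity to complete jointly normal with correlation r.
- Mean propensity among the retained 80% = φ(−0.8416)/0.8 = 0.350 SD.
- Spurious difference = 0.350 × r. For r = 0.2 this is 0.07 SD; for r = 0.3, 0.105 SD; for r = 0.5, 0.17 SD (0.17498).
- On the planning SD of 1.762, r = 0.2 to 0.5 gives about 0.12 to 0.31 MoCA points.
- With 35 against 44 and an unchanged SD, two-sided type I error is 5.0% at r = 0, 5.3% at r = 0.1, 7.4% at r = 0.3 and 11.9% at r = 0.5.

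**5. How far this depends on control loss.** Suppose controls are also lost in an outcome-related way with the same r.
- 20% control loss: 0.350 − 0.350 = 0, so no spurious difference.
- 10% control loss: φ(−1.2816)/0.9 = 0.195; 0.350 − 0.195 = 0.155; times 0.2 to 0.5 gives about 0.03 to 0.08 SD.

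**6. How far it depends on the contrast.** The figures in steps 4 and 5 concern the post-intervention level. The planned repeated-measures ANOVA includes baseline. In its group-by-time contrast, selection on a stable level cancels and only selection related to change remains.

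**The case against.** The best defence is that nobody would apply the rule literally. The sentence follows a plan for between-group comparisons in a two-arm trial, and the natural meaning is programme completion for those assigned to it and assessment completion for everyone. An article may also leave arm-specific definitions to a fuller document. The first part is fair, and the probable reading is taken seriously above. The second does not dispose of the point: the article does not leave the definition open but states one, and the one stated does not fit the design. The probable reading still filters adherence on one side.

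Several stronger inferences are tempting, and the objection to each stands:
- **That controls are unselected.** They are not; the outcome-assessment condition applies to them too. Only the additional programme condition is asymmetric.
- **That 20% is the SIACI non-completion rate.** The protocol applies 20% attrition to both groups and gives no non-completion rate. The illustration borrows the figure.
- **That bias towards SIACI is established.** The documents give neither the correlation nor its sign. Better outcomes among completers are plausible in a sample running from subjective decline to mild AD. But the Intervention group section matches groups to ability and adapts difficulty, which could weaken the link.
- **That the 0.07 to 0.17 SD is the bias of the planned analysis.** Control loss and the use of baseline both reduce it.

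One might also read the Waitlist control group section as allowing controls to start after week 16, before the 6-month visit. The abstract places it after follow-up, and on either reading no control has completed SIACI by the post-intervention assessment.

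**Conclusion.** The concern holds as a defect in a stated rule. That the rule cannot be applied to the waitlist arm follows from the text and rests on no assumption. That the probable reading filters on adherence in one arm only also follows from the text.

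The size of the resulting bias is unknown. Its likely direction, in favour of SIACI, is a judgement that those who complete tend to do better. The range of 0.07 to 0.17 SD is an upper-end illustration under the assumptions listed, and moves towards zero as they are relaxed.

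A reader might infer that the trial's main conclusion is at risk. The documents do not support that: intention-to-treat with multiple imputation is the main analysis, and neither it nor the sample size depends on the per-protocol set. What is weakened is the only robustness check the article names. It should be corrected, at modest severity.

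**What to change.** State the per-protocol set by arm:
- SIACI: attendance at or above a threshold fixed before unblinding, with the relevant assessment completed.
- Control: no SIACI exposure before the assessment, with the same assessment completed.

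Adjust this comparison for baseline score and diagnostic stage. The article's examples of adjustment variables (age, gender, education, if necessary) name neither. Say plainly that adherence selection may remain.

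In place of this comparison, or beside it, estimate the complier-average causal effect with randomisation as the instrument. Because controls have no access to SIACI before follow-up, the estimate is the intention-to-treat difference divided by the proportion of the SIACI arm that completes. At an assumed 80% completion that multiplies the difference, and approximately its interval width, by 1/0.8 = 1.25. It keeps the randomised comparison, so a programme with no effect gives an expected estimate of zero whatever the link between completion and outcome. It assumes that assignment has no effect on those who do not complete. Partial attendance could breach this, so the threshold needs thought.

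The cost is a few sentences, a little more analysis and wider intervals. The completion status needed is the one the existing rule already requires. The Intervention group section plans a per-participant log at each session; it does not mention attendance by name, so the log should be confirmed to record it.
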